## Abstract

**Background:**

Preterm birth or low birth weight is the single largest cause of death in newborns, however this mortality can be reduced through newborn care interventions, including Kangaroo Mother Care (KMC). Previously, a multi-country randomized controlled trial, coordinated by the World Health Organization (WHO), reported a significant survival advantage with initiation of continuous KMC immediately after birth compared with initiation of continuous KMC a few days after birth when the baby is considered clinically stable.

Whether the survival advantage would lead to higher rates of neurodevelopmental morbidities, or the immediate KMC will also have a beneficial effect on cognitive development also, has not been investigated. We therefore propose to test the hypothesis that low-birth-weight infants exposed to immediate KMC will have lower rates of neurodevelopmental impairment in comparison to traditional KMC-treated infants, by prospectively following up infants already enrolled in the immediate KMC trial for the first 2 years of life, and assessing their growth and neurodevelopment.

**Methods:**

This prospective cohort study will enroll surviving neonates from the main WHO immediate KMC trial. The main trial as well as this follow-up study are being conducted in five low- and middle-income countries in South Asia and sub-Saharan Africa. The estimated sample size for comparison of the risk of neurodevelopmental impairment is a total of 2200 children. The primary outcome will include rates of cerebral palsy, hearing impairment, vision impairment, mental and motor development, and epilepsy and will be assessed by the age of 3 years. The analysis will be by intention to treat.

**Discussion:**

Immediate KMC can potentially reduce low-birth-weight-associated complications such as respiratory disease, hypothermia, hypoglycemia, and infection that can result in impaired neurocognitive development. Neuroprotection may also be mediated by improved physiological stabilization that may lead to better maturation of neural pathways, reduced risk of hypoxia, positive parental impact, improved sleep cycles, and improved stress responses. The present study will help in evaluating the overall impact of KMC by investigating the long-term effect on neurodevelopmental impairment in the survivors.

**Trial registration:**

Clinical Trials Registry-India CTRI/2019/11/021899. Registered on 06 November 2019.

Trials registration of parent trial: ACTRN12618001880235; Clinical Trials Registry-India: CTRI/2018/08/015369.

## Background

Nearly, 15.5% of all births, or more than 20 million infants worldwide, are born with low birth weight (LBW) as a result of preterm birth or intrauterine growth restriction or both [1, 2]. Preterm birth or LBW is the single largest cause of death in newborns, but the mortality can be reduced by effective newborn care interventions. However, for years, it was demonstrated that although mortality was being improved by interventions for LBW newborns, the impact on morbidity, including neurocognitive impairment and motor disabilities, was unchanged [3]. More recently, there is evidence suggesting that infant survival with improved neurodevelopmental outcomes is increasing slightly and is associated with both improved medical interventions and maternal factors [4]. However, there is also a concern of an increased risk of neurodevelopmental impairment, and this enigma needs to be addressed by a systematic study. Therefore, while evaluating the impact of any intervention on mortality in this population, it is equally important to study the risk of neurodevelopment impairments, including cerebral palsy, hearing and vision impairment, cognitive impairment, and epilepsy.

The World Health Organization (WHO) defines Kangaroo Mother Care (KMC) as a technique used in preterm and LBW infants of continuous skin-to-skin contact between mother and baby until the infant shows signs of intolerance. Exclusive breastfeeding is also encouraged as an essential component of KMC. Notably, however, it is currently recommended that continuous KMC should be initiated only once the baby is stable, meaning that the baby must be breathing spontaneously without additional oxygen [5].

“WHO recommendations on interventions to improve preterm birth outcomes” recommends KMC for the routine care of newborns weighing 2.0 kg or less at birth, which should be initiated in health care facilities as soon as the newborns are clinically stable [6]. These babies should be provided as close to continuous KMC as possible. Intermittent KMC, rather than conventional care, is recommended for newborns weighing 2.0 kg or less at birth, if continuous KMC is not possible [6]. There is no current recommendation for KMC for unstable < 2.0 kg neonates. A recently updated Cochrane review reported 40% lower mortality in infants with birth weight < 2.0 kg given KMC compared to mortality in those who were given standard care in hospitals, at 40 to 41 weeks postmenstrual age [7]. In almost all studies included in the Cochrane review, KMC was initiated after the baby was clinically stable, with the median age at initiation of KMC 3.2 to 24.5 days [7]. Two randomized controlled trials (RCTs) comparing immediate versus conventional KMC from South Africa and Vietnam [8–10] showed favorable results for immediate KMC initiation. This data led the World Health Organization to coordinate a multi-country randomized controlled trial to evaluate the effect of initiating continuous KMC immediately after birth on survival (compared with initiation of continuous KMC a few days after birth when the baby is considered clinically stable). This RCT assessed newborn survival outcomes over the acute hospital period up to a 28-day follow-up [11]. The study enrolled 3211 infant-mother dyads with 1609 dyads in the intervention arm and 1602 in the control arm. The median daily duration (hours) of skin-to-skin contact was 16.9 h (IQR 13.0–19.7) in the intervention and 1.5 h (IQR 0.3–3.3) in the control arm. Neonatal death occurred in 12.0% and 15.7% infants, respectively, in the two arms (RR 0.75; 95% CI 0.64–0.89; *p* = 0.001). The study concluded that in infants with birth weight between 1.0 and < 1.8 kg, immediate KMC (versus conventional KMC care) resulted in a significant reduction in neonatal mortality [12]. However, in order to evaluate the overall impact of KMC, the long-term effect on neurodevelopment in the survivors should be assessed.

It has been observed that KMC can reduce bradycardia and oxygen desaturation events in preterm infants, providing physiological stability and possible benefits for neurodevelopmental outcomes [13]. Few studies involving KMC initiated in stable infants show that KMC has a beneficial effect on both short-term [14] and long-term [15, 16] neurodevelopmental outcomes of preterm and LBW babies compared to no KMC. The long-lasting social and behavioral protective effects have been observed beyond 20 years after the KMC intervention [17].

Studies have suggested that there is a positive impact of KMC on parental interaction due to not only increased skin-to-skin contact but also increased opportunity for bonding through breastfeeding and, as a result, impact on the child’s behavior, which can be long lasting. However, the degree of direct impact on cognition, language, motor, auditory, and vision impairment has not been consistent, although most studies do demonstrate a positive trend in these domains [17–21]. Furthermore, emerging evidence from smaller studies suggests that, in addition to the positive parental impact, the implementation of KMC may also be neuroprotective through both improved sleep cycles and brain maturation patterns seen on EEG [22, 23], as well as improved stress responses in general, which had a lasting impact when reviewed over a 10-year period on both emotional and cognitive development [24].

Despite the evidence of the benefit of KMC after stabilization on neurodevelopmental outcomes, an evaluation of the long-term effects of the KMC initiated immediately after birth on the risk of neurodevelopmental impairment such as motor or sensory impairment or cognitive deficits is not well known.

We hypothesize that KMC initiated immediately after birth can improve physiological stabilization and potentially lead to anatomical or functional changes in the brain in the neonatal period, thus allowing for better maturation of the brain and pathways leading to a possible decrease in neurocognitive morbidity as well as reduce the risk of hypoxia, thus decreasing long-term morbidity. In addition, given the positive impact of traditional KMC on parental bonding, it is argued that the earlier KMC is initiated (e.g., with immediate KMC), the stronger the bond, leading to better family motivation and stimulation and thus positively impacting on child development.

The main outcome of interest for the parent study on immediate KMC was the impact on neonatal mortality [11, 12]. Evidence of the longer-term effect of the intervention on the risk of neurodevelopmental impairment, growth, and mortality beyond the neonatal period, on the other hand, will provide additional evidence and rationale for policy change as the intervention targets survival as well as helping babies to thrive.

We therefore propose to follow up the newborns enrolled in the recently published immediate KMC study [11, 12], beyond the neonatal period up to 3 years of age to additionally study the risk of neurodevelopmental impairments, specifically the risk on growth, feeding, caregiving practices, mortality, and home environment. Our main hypothesis is that those newborns who were provided continuous KMC initiated immediately after birth will experience a reduced risk of neurodevelopmental impairment, including the risk of cerebral palsy, hearing impairment, vision impairment, mental and motor impairments, and epilepsy, compared with a similar group in whom KMC was initiated only after stabilization.

## Methods

### Study design

This is a prospective cohort study of the children already enrolled in the immediate KMC randomized controlled trial to evaluate the impact of continuous Kangaroo Mother Care initiated immediately after birth (iKMC) on survival of newborns with birth weight between 1.0 and < 1.8 kg [11, 12].

### Study setting

As this study is a follow-up of the concluded and recently published iKMC trial [12], the study is being conducted at the same five LMIC study sites encompassing hospitals in Ghana, India, Malawi, Nigeria, and Tanzania. The selected facilities are tertiary care hospitals that care for small and sick newborns with a high proportion of LBW babies and follow-up high-risk newborns. As part of standardization across the involved study sites, prior to the study, trainings and standardization assessments were done to ensure all participating sites could offer the WHO minimum package of care for small and sick newborns [11].

### Study population

All infants born with birth weight between 1.0 and < 1.8 kg, enrolled in the main trial, who survive the neonatal period, and whose parents consent for their participation in the follow-up study, are eligible to be enrolled.

All infants who die within the first month of life or whose parents refuse consent for follow-up will be excluded from the study.

We employ two strategies to approach the parents for enrolment. First, we approach the mother/parent during the 29-day follow-up visit for the main trial. The second strategy is for children who have completed the 29-day follow-up visit in the main trial. For these children, we approach the mother/parent either telephonically or when they visit the high-risk infant follow-up clinic as part of standard hospital care. A verbal preconsent is taken and an in-person hospital visit is scheduled for a detailed written informed consent for participation in the follow-up study.

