### Sample size calculation

The sample size for the main iKMC trial was a total of 4200 neonates. Early completion in January 2020 led to a total of 3211 neonates being enrolled in the main iKMC trial. A preliminary review of literature of neurodevelopment in infants between 1 and < 1.8 kg shows the prevalence of any of the conditions of cerebral palsy, hearing impairment, vision impairment, and mean development scores to vary from 5 to 25% [25–27]. Any neurodevelopmental impairment (e.g., cerebral palsy, Bayley score < 85, hearing or vision impairment) in the study population is estimated to be approximately at 15–25%. We estimated the sample size for comparison of the risk of neurodevelopmental impairment in control and intervention groups (20% compared with 15% or 25% [25% lower or higher]) with 80% power and a significance level of 5% to be 1100 per group, requiring a total of about 2200 children.

We thus propose to enroll 2200 babies from the main trial to reach the above-mentioned sample size.

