### Primary and secondary outcomes

The primary outcome of the follow-up study is the presence of neurodevelopmental impairments assessed by the age of 3 years in all enrolled children. The study duration and window for the last outcome assessment were extended from 2 to 3 years after ethics approval, due to the COVID-19 pandemic. Specifically, this composite outcome includes rates of motor impairment and risk of cerebral palsy, hearing impairment, vision impairment, cognitive, language, motor, socio-emotional or adaptive behavior, and epilepsy and the presence of any one or more will be considered as neurodevelopmental impairment. Secondary outcomes include growth and feeding practices, mortality and home environment (maternal depression and parent–child interactions), and rates of overnight hospital admissions.

Outcomes are assessed via standardized tools and questionnaires (Table 1). Motor impairment and risk of cerebral palsy are measured by standardized neurologic evaluation, using a validated tool, Hammersmith Infant Neurological Examination (HINE) at 6 months, 1 year, and 2 years of age. Cognitive, language, motor, socio-emotional, or adaptive behavior is assessed using Bayley Scales of Infant and Toddler Development (BSID III) at 2 to 3 years of age. Epilepsy is diagnosed using a standardized questionnaire, with operationalization of the International League against Epilepsy (ILAE) definition. Hearing is evaluated at discharge from the hospital or as soon as possible after enrolment in the follow-up study. First, an assessment by screening auditory brainstem responses (ABR) is performed at the facility. If the infant clears this assessment, no further assessment for hearing is required. In case the infant fails this initial screening, he/ she is referred to the audiologist or specialist for re-screening including a diagnostic ABR if required. Visual acuity is measured using Teller Acuity Cards, at or any time after 1 year of age at the facility.

**Table 1 Tab1:** Outcome measurements

Outcomes	Tool	Measurement strategy	Rationale

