### General principles for analysis

The analysis will be by intention to treat. The primary outcome is a composite outcome comprising cerebral palsy, hearing impairment, vision impairment, cognitive, language, socio-emotional, adaptive and motor impairment, and epilepsy, and the presence of any one or more will be considered as neurodevelopmental impairment. However, during analyses, we will also consider each of these outcomes individually. Table 1 includes the scale/tool used for outcome measurement and wherever appropriate, the cutoffs of the scales, to indicate the presence or absence of the neurological impairment.

The primary and secondary outcomes will be compared between the intervention and control groups. All planned analysis will use a 5% significance level. Risk ratios and their confidence intervals will be calculated and will be the primary analysis if the loss to follow-up is 2.5% or lower. In case the loss to follow-up for the primary outcome is greater than 2.5%, we will additionally calculate hazard ratios and their confidence intervals. Additionally, we will adjust the results for confounding using multiple logistic regression and Cox proportional hazards models if there are any important differences in baseline characteristics between immediate KMC and control groups.

If more than 5% of data is missing from interim assessments, multiple imputation will be performed, accounting for clustering by country with the number of imputations based on the percentage of missing data. Subgroup analysis will be conducted by (i) birth weight categories (1 to < 1.2 kg, 1.2 to < 1.5 kg, and 1.5 to < 1.8 kg), (ii) gestation (< 34, 34–36, >=37 weeks), and (iii) singleton/multiple birth. Secondary analysis will be limited to an analysis by compliance. This secondary analysis will present the efficacy of the intervention by average duration of skin-to-skin contact over the first 3 days of life, categorized as > =20 h/day, 10–19 h/day, and < 10 h/day.

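### The analysis labelled intention to treat covers only consenting survivors of a trial whose intervention changed survival, so randomisation no longer fully protects the impairment comparison

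*Protocol article*

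**What the plan says.** - **Label.** General principles for analysis: "The analysis will be by intention to treat". The Methods part of the abstract says the same.
- **Who is analysed.** Study population: "All infants who die within the first month of life or whose parents refuse consent for follow-up will be excluded from the study". Enrolment needs both survival of the neonatal period and parental consent.
- **What happened before enrolment.** Background: "The study enrolled 3211 infant-mother dyads with 1609 dyads in the intervention arm and 1602 in the control arm". It then reports: "Neonatal death occurred in 12.0% and 15.7% infants, respectively, in the two arms". It concludes that immediate KMC "resulted in a significant reduction in neonatal mortality".
- **Where death is counted.** The primary composite consists of impairments only. On death, Primary and secondary outcomes states: "Secondary outcomes include growth and feeding practices, mortality and home environment". Table 1 counts death from 29 days to 3 years, in enrolled children only.
- **Other analyses.** General principles for analysis plans adjustment if baseline characteristics differ importantly, and subgroups by birth weight, gestation and multiplicity. As worded, it confines secondary analysis to one by compliance, meaning duration of skin-to-skin contact.

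**The concern.** An intention-to-treat comparison keeps everyone who was randomised. Here the analysed set is defined by two later events, and the document's own figures show that the intervention altered one of them. The two groups of survivors therefore need not be alike in frailty, even though allocation was random. The second event, consent, was sought after an unblinded parent trial and, for many families, well after day 29. Children who enrol late must also have survived until then.

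The abstract asks two things: whether better survival brings more neurodevelopmental morbidity, and whether immediate KMC itself benefits development. A risk ratio among survivors cannot by itself separate an effect on the developing child from a change in which children are alive to be assessed. The Background wants the results to support policy change, so the label affects how a null or adverse result would be read.

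**Working it through.** **1. The plan's own sample size.** The Sample size calculation section compares 20% with 15% or 25% "with 80% power and a significance level of 5% to be 1100 per group, requiring a total of about 2200 children". I assumed a two-sided test, pooled variance and 1:1 allocation:

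n = [1.96·√(2·p̄·(1−p̄)) + 0.8416·√(p₁(1−p₁) + p₂(1−p₂))]² / (p₁−p₂)²

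- 20% against 25%: p̄ = 0.225, so n = (1.1575 + 0.4961)² / 0.0025 ≈ 1094 per group. This reproduces 1100.
- 20% against 15%: 906 per group.
- Power at 1100 per group: 80.2% for 20% against 25%, and 87.0% for 20% against 15%.

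**2. Expected survivors**, from the arm sizes and mortality in the Background:

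- Intervention: 1609 × 0.880 ≈ 1416.
- Control: 1602 × 0.843 ≈ 1350.
- Total ≈ 2766. The target of 2200 is 2200/2766 = 79.5% of survivors and 2200/3211 = 68.5% of those randomised. About 566 survivors would not be enrolled.

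**3. Extra survivors.** Assume the intervention caused no deaths. Then 15.7% − 12.0% = 3.7% of intervention infants (about 60) survived who would have died under control. As a share of intervention survivors, f = 0.037/0.880 = 4.2%.

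**4. Effect on the survivor comparison.** Let q be the impairment risk of the extra survivors. The documents give no figure, so q is assumed and shown as a range. Control risk is 20%, and r is the intervention-arm risk among children who would survive in either arm.

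Observed intervention risk = (1−f)·r + f·q

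| q | No true effect (r = 20%): observed risk | RR | Chance of significant harm result (nominal 2.5%) | True benefit (r = 15%): observed risk | RR | Power |
|---|---|---|---|---|---|---|
| 30% | 20.4% | 1.02 | 4% | 15.6% | 0.78 | 76% |
| 40% | 20.8% | 1.04 | 7% | 16.1% | 0.80 | 67% |
| 50% | 21.3% | 1.06 | 11% | 16.5% | 0.82 | 57% |
| 100% (ceiling) | 23.4% | 1.17 | 48% | 18.6% | 0.93 | 13% |

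Chances and power are at 1100 per group. For q from 30 to 50% the shift under no effect is 0.042 × (q − 0.20) = 0.4 to 1.3 points, at most a quarter of the 5-point difference planned for. If q were 10%, the RR under no effect would be 0.98, a bias in favour of the intervention.

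**5. Death or impairment over all randomised infants** (neonatal deaths only, 20% impairment in control survivors):

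- Control: 0.157 + 0.843 × 0.20 = 32.6%.
- Intervention, no difference in impairment: 0.120 + 0.880 × 0.20 = 29.6% (RR 0.91).
- Intervention, 15% impairment: 0.120 + 0.880 × 0.15 = 25.2% (RR 0.77).
- Break-even: (0.3256 − 0.120)/0.880 = 23.4% impairment in intervention survivors.

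**The case against.** The strongest reply is that the article is open about its target. It calls the design a prospective cohort study, enrols surviving neonates, and speaks of effects in the survivors. Impairment cannot be measured in infants who died. For the abstract's first question, whether better survival brings more morbidity, the impairment rate among survivors by arm is a direct answer, and any excess in the extra survivors belongs to it. Neonatal mortality by arm is already published, later mortality is a secondary outcome, and the sample size allows for either direction. All of this stands, and it is why the survivor comparison should remain primary. It does not rescue the label. Conditional adjustment for baseline differences and the planned subgroups address measured frailty only in part.

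A reader might go further in three ways that the documents do not support.

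- **That the comparison is simply not randomised.** Allocation was randomised. What is lost is full protection once the analysis conditions on survival and consent.
- **That a protective effect of the planned size could appear as harm.** Even if every extra survivor were impaired, a true RR of 0.75 would be observed as at most 0.93.
- **That no analysis anywhere combines death with impairment or bounds the survivor effect.** Only the condensed article is at hand, and such analyses are commonly left to an analysis plan. What can be said is that the article's wording on secondary analysis, as it stands, leaves no room for them.

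**Conclusion.** The point holds in a limited form. The intention-to-treat label is wrong as written, because the analysis keeps only consenting survivors of a trial in which the intervention changed neonatal survival, and death lies outside the primary composite. That follows from the document alone.

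The size of the resulting bias is modest and rests on assumptions: that the intervention caused no deaths, that 20% of control survivors are impaired, and that the extra survivors carry a 30 to 50% risk. Under these the null RR moves to between 1.02 and 1.06, and a true RR of 0.75 is diluted to between about 0.78 and 0.82. That the extra survivors are frailer is plausible but not shown, and the direction would reverse if they were at lower risk. Selection through consent and late enrolment is additional and cannot be quantified from the document.

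**What to change.** 1. In the abstract and in General principles for analysis, replace the intention-to-treat label with a description such as: by allocated group among consenting survivors. Keep this as the primary analysis.
2. Amend the sentence that limits secondary analysis to compliance.
3. Add a supportive analysis of death or impairment by allocated group over all 3211 randomised infants. Use neonatal deaths from the parent trial, and weighting or multiple imputation for survivors who were not enrolled. Report death and impairment separately beside the combined result.
4. Bounds on the effect in children who would survive in either arm are optional and could go in the analysis plan.

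**Cost.** Items 1 and 2 are wording. Item 3 needs no new visits, but it is more than linkage to parent-trial data. Deaths after day 29 are recorded only for enrolled children, so about 566 survivors (if 2200 enrol) lack both later vital status and impairment status, some of them because their parents refused consent. The result therefore leans on missing-data assumptions. The combined endpoint is also partly driven by the mortality result already known: with no difference in impairment (29.6% against 32.6%) and complete data on about 1600 per arm, it would favour the intervention significantly about 44% of the time. That is why it should be supportive and its two parts shown.
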